### 7.3 Analytical procedures

Change in the endpoint well-being (as total score) and the intermediate outcomes dietary habits, physical activity, and mental health, will be analysed across time and between groups using mixed model for repeated measures, and reported as estimates with confidence intervals. The model will include intervention level and time (0, 6, 12, 18 and 24 months).

To investigate correlations and associations of demographic factors and user engagement with behavior change, mental balance, and well-being, structural equation modelling and mixed models will be applied.

Regression analysis and mixed models will be applied to evaluate mediating factors and responsiveness. These analyses will explore if high levels of motivation, self-efficacy and reduced perceived barriers mediates improvements in reaching the self-identified goal, behavior, mental health, and well-being and whether improvements in motivation, behavior, and mental health mediate well-being. Cut off values for the intermediate outcomes will be derived based on baseline values and findings from similar studies.

The threshold for statistical significance will be set at  $p < 0.05$ .

Qualitative data (chat groups and dialogues with included actors) will be analyzed by content analysis (46).

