This study is a real-world post-market observational clinical investigation with a control group aimed to evaluate the impact of a digital service in improving well-being by supporting healthy lifestyle habits. A four-armed control condition will allow comparison between a control group recruited among the general population, and three levels of intervention among subscribers. The levels of intervention are I) core functions include self-monitoring, goal setting, action planning, an AI chat and databases with recipes and exercises; II) the same core functions + social support; II) the core functions + social support + individual counselling by a professional health coach. Randomisation of subjects to the different allocation arms is not appropriate because the users or their employers will pay for the digital service and thus choose the level of support.

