## 6. Design of the clinical investigation

### 6.1 Investigational device/Description of exposure

The medical device to be investigated is the mobile phone application (app) LongLife Active®. The app includes three core topics: 1) Healthy diet, 2) Physical activity, and 3) Mental balance. Supplement 4 shows the included intervention components and behavior change techniques. The service includes functions such as tracking and self-monitoring behavior and health outcomes, goal setting, action planning, a database with food recipes, a database with exercises, a database with relaxation exercises, skills training articles and webinars, live events, adjustable push notifications and gamification (rewards). If the user prefers there are options to pay extra for further social support: a version including a community (chat groups and group coaching sessions, live events and physical meetup events), and a version including the community plus the possibility to have a private health coach. The app is assisted by artificial intelligence to direct the support to the individual timely and based on the needs, motivation, preferences, experiences, opportunities, and capabilities of each user. The user decides which functions to use.

The literature review undertaken during the formative phase showed participants wished for interface design and reminders to be customizable, and that the service should be integrated with other services (such as shopping lists). These are examples of aspects that have been regarded to keep engagement over time. With a straightforward design, illustrations, and short video instructions the service is customized for people with low skills in the Swedish language or with low digital and/or health literacy.

No other medical devices or medications are to be used.

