## 6.2 Subjects

### 6.2.1 Recruitment

The medical device will be launched and promoted by the company LongLife Active AB as a real-world project. The ambition is to reach individuals in need of lifestyle change, with a special emphasis on hard-to-reach groups. Health care services, pharmacies, employers, benefit platforms (e.g. Benify and Epassi) and social media will be targeted. Employers may apply for the health promoting subsidy, Friskvårdsbidrag, when employees sign up for LongLife Active. Health care patients prescribed physical activity (Fysisk aktivitet på recept, FaR) from their care provider is allowed a reduced fee on the membership of LongLife Active®.

Individuals who sign up for the service from September 2023, or as soon as ethical approval is obtained, will be informed about the research study and invited to consent for data extraction. Controls will be recruited through social media at the same time frame.

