#### *Reach*

Information on promotion channels and data on sales statistics will be collected from the provider. This data is not connected to the subjects. Demographics: age, gender, occupational status, profession, education, country of origin and living area, as well as a question on how the subject got information about the service will be collected by questions when signing up.

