## 13. Informed consent process

Individuals who sign up for the digital service LongLife Active from October 2023 (or as soon as ethical approval is obtained) will be informed about the research study (informed consent in supplement 5a) and invited to consent for data extraction in the app. Controls will be recruited through social media and through large companies and will be sent the detailed information by email (supplement 5b). Control subjects consent in the survey tool before starting to answer the questionnaire.

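### Where employers set the support level or companies supply controls, the well-being model may give intervals that are too narrow, and no listed variable identifies the employer

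*Protocol*

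**What the plan says.** **Who sets the exposure.** Section 3.1 rules out randomisation because "the users or their employers will pay for the digital service and thus choose the level of support". Section 6.2.1 lists the recruitment channels: "Health care services, pharmacies, employers, benefit platforms (e.g. Benify and Epassi) and social media will be targeted".

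**Where controls come from.** Section 13 says "Controls will be recruited through social media and through large companies". Section 6.2.1 says "Controls will be recruited through social media at the same time frame" and does not mention companies. Both are current text.

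**The model.** Section 7.3 names a mixed model for repeated measures and adds: "The model will include intervention level and time (0, 6, 12, 18 and 24 months". Section 7.4 sizes the study on independent subjects, with no ICC or design effect.

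**What is recorded.** The Reach paragraph of section 6.3.2 lists "Demographics: age, gender, occupational status, profession, education, country of origin and living area", plus a question on how the subject heard of the service. Table 1 repeats the demographic items and adds no employer, payer or recruiting company. For promotion-channel and sales data, Reach says "This data is not connected to the subjects". The full case report form is in supplement 6, which is not shown.

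**The concern.** Where an employer picks Basic, Standard or Premium for its staff, the exposure is assigned to a group of colleagues rather than to one person. Where a company supplies controls, those controls are colleagues too. They share workload, management and morale, all of which can bear on well-being. A model whose only correlation structure is within the person then counts colleagues as independent and overstates the information in each between-group contrast.

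Two contrasts are exposed: the level comparison in Hypothesis 2 and the primary comparison of users with controls. The second depends almost entirely on the control group, which is planned at 200 against 5000.

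The data-capture side matters as much as the model. An analysis plan can add a random effect or robust errors later, but only if someone recorded which subjects belong together.

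**Working it through.** **Inputs from the protocol.** SD 19.9, two-sided alpha 0.05, difference 12 points, 75% drop-out at 6 months and 20% excluded for a baseline score above 70 (section 7.4); enrolment 5000 users and 200 controls (section 6.2).

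**Assumptions, not in the protocol.** ICC of the 6-month score 0.01 to 0.05; m evaluable subjects per employer, 5 to 20; share s of subjects in such clusters, 6% to 100%. Applying the 75% and 20% losses to controls is also an assumption.

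**The plan's own figure.** There is no clustering figure to reproduce. The recruitment inflation reproduces: 25/(0.25 × 0.80) = 125 per group, and 4 × 125 = 500. It contains no allowance for clustering. (The 25 per group does not follow from the stated inputs, which give 58 for a two-sample comparison of 12 points. That is a separate matter.)

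**Evaluable numbers.** Users: 5000 × 0.80 × 0.25 = 1000, about 333 per level if equal. Controls: 200 × 0.80 × 0.25 = 40.

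**Level contrast, employer sets the level.** Design effect DEFF = 1 + s(m − 1)ICC; true error = 2[1 − Φ(1.96/√DEFF)].

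| Share s | ICC | m = 5 | m = 10 | m = 20 |
|---|---|---|---|---|
| 6% | 0.05 | 5.1% | 5.3% | 5.7% |
| 25% | 0.01 | 5.1% | 5.3% | 5.5% |
| 25% | 0.05 | 5.6% | 6.3% | 7.8% |
| 50% | 0.01 | 5.2% | 5.5% | 6.1% |
| 50% | 0.05 | 6.2% | 7.7% | 10.7% |
| 100% | 0.01 | 5.5% | 6.0% | 7.2% |
| 100% | 0.05 | 7.4% | 10.4% | 16.0% |

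Worked example, s = 0.5, m = 20, ICC 0.05: DEFF = 1 + 0.5 × 19 × 0.05 = 1.475; 1.96/√1.475 = 1.614; error 10.7%. The 6% row takes the whole remainder of the pilot's 94% social-media recruitment (section 3.3) as employer-sourced.

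**Level contrast, colleagues choose different levels.** In a simulation of 66 employers with 10 subjects each at ICC 0.05 (4000 runs), coverage of the naive 95% interval was 90.3% when the employer set the level and 95.1% when colleagues were spread evenly over levels.

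**User-versus-control contrast.** Under independence the variance factor is 1/1000 + 1/40 = 0.0260, of which controls contribute 0.0250/0.0260 = 96%. Take ICC 0.05 and half of users in clusters of 10, so the user DEFF is 1 + 0.5 × 9 × 0.05 = 1.225:

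- Half of controls in four companies of 5: control DEFF 1.10; factor 1.225/1000 + 1.10/40 = 0.0287; ratio 1.105; error 6.2%.
- All controls in four companies of 10: control DEFF 1.45; factor 0.0375; ratio 1.44; error 10.3%.
- Half of controls in one company of 20: control DEFF 1.475; factor 0.0381; ratio 1.47; error 10.5%.

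Power for 12 points is 96.2% under independence (SE = 19.9 × √0.0260 = 3.21). With valid errors it is 94.5%, 87.6% and 87.1% in these three cases.

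**The case against.** A reader might infer that the intervals are too narrow as a matter of fact. The protocol does not support that. The effect needs a positive ICC, sizeable clusters and a substantial employer share, and none of these is given. The only recruitment mix on record, the pilot's, was 94% social media; at that share the error stays below 6%. The heavier scenarios are also demanding. With 20% of recruits evaluable, 20 evaluable colleagues means about 100 consenting recruits from one employer, and 20 of 40 evaluable controls from one company means about 100 of the 200. This stands and limits the size. The pilot mix may not carry over, though, because section 6.2.1 now targets employers and benefit platforms.

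Much of the text points to personal choice of level: sections 2.2 and 6.1 describe users signing up and paying extra if they wish. This stands for the level contrast. It does not protect the control contrast.

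Section 7.3 speaks of change, with month 0 in the model. A stable workplace effect would largely cancel in change. This stands in part, but Hypothesis 1 concerns the 6-month mean score, and effects that vary over time would not cancel.

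A reader might also infer that employer is definitely not recorded. Supplement 6 is not shown, so one can say only that it is not among the listed variables. The sentence on unlinked data concerns promotion channels and sales statistics, not sign-up records.

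Finally, random effects and robust errors are normal content for an analysis plan. That is fair for the model term. It does not cover an identifier that was never captured.

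One extension should not be pressed. Standard and Premium users share "chat groups and group coaching sessions, live events and physical meetup events", which could add correlation of its own, but the protocol does not say that a coach or group identifier is logged, and the effect has not been sized.

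**Conclusion.** The point holds in conditional form. Where employers choose the level or companies supply controls, the stated model leaves correlation between colleagues out, and intervals may be too narrow. Under an assumed ICC of 0.01 to 0.05, the true error at nominal 5% is about 5 to 6% with few employer-sourced subjects or small clusters. At ICC 0.05 with half or more of subjects in groups of 10 to 20, it is about 8 to 16% for the level contrast when the employer sets the level. For the control contrast the range examined is 6.2 to 10.5%. There is no inflation at ICC zero, and none for level contrasts when colleagues spread evenly over levels.

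The firmest parts do not depend on an ICC. The listed variables contain nothing that identifies the employer or recruiting company, and sections 6.2.1 and 13 disagree on where controls come from. This is a worthwhile, inexpensive improvement; it does not show that the primary analysis is invalid.

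**What to change.** 1. **Data capture (section 6.3.2 and Table 1).** At month 0, record a pseudonymised employer or payer code for users and a recruiting-company code for controls, linked to subject ID. Use one coding scheme for both, so that a company supplying users and controls is recognised. State in the Reach paragraph that this code is an exception to the unlinked sales data. If supplement 6 already holds such a code, refer to it.
2. **Model (section 7.3).** Use cluster-robust standard errors with a small-sample correction, or a random intercept for employer or company, with an employer-by-time term if change is the estimand. Treat self-paying users and social-media controls as their own clusters.
3. **Coach or group.** Use an identifier in a sensitivity analysis for Standard and Premium only if one is available.
4. **Control source.** Make sections 6.2.1 and 13 agree. If companies are used, spreading controls over several limits the effect: a correction cannot recover much from one or two large clusters.

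The cost is one code per subject, one model term or error option, and a short data-protection addition to the participant information. Intervals will be slightly wider where colleagues cluster. The change itself calls for no extra recruitment, although in the heavier control-clustering scenarios valid power is about 87 to 88%, just under the planned 90%. If the ICC proves near zero, almost nothing is lost.

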## **1.6 Overall synopsis of the clinical investigation**

*Study design:* Post-market observational clinical investigation with a control group (a quasi-experimental study). The project also includes implementation and longitudinal studies.

*Inclusion criteria (intervention arms):* Adults  $\geq 18$  years who sign up for the service LongLife Active using BankID for identification, and consent to the research study.

*Inclusion criteria (controls):* Adults  $\geq 18$  years.

- *Exclusion criteria (intervention arms):* Individuals who are discharged from the app due to refracting the terms of the service will be excluded. Subjects scoring  $>70$  on well-being or subjects who appear as friends, colleagues, or family with anyone in the research or owner group will be excluded from the primary analyses.
- *Exclusion criteria (controls):* Age  $\leq 17$  years. Is currently using a digital product or any other kind of support for behavior change (e.g. Livsstilsverktyget, Health Integrator, Weight Watchers). Is found to be a user of LongLife Active. Subjects scoring  $>70$  on well-being or subjects who appear as friends, colleagues, or family with anyone in the research or owner group

will be excluded from the primary analyses.

*Number of subjects:* Intervention: 5000, Controls: 200

*Duration of the intervention:* the subjects will be followed up to 24 months.

*Follow-ups:* 3, 6, 12, 18, and 24 months

*Objectives:* The aim of this project is to evaluate the effectiveness of an individually tailored digital service aimed to support healthy habits on well-being among the adult population compared to a control sample of the general population.

Secondary objectives are to describe the internalization of the digital service, to evaluate the impact of the digital service on reaching self-identified goals, behavior change, and mental health, and to explore predicting and mediating factors for responses.

*Primary endpoint:* Well-being at 6 months

*Secondary (intermediate) endpoints:* Achieving self-identified goals, dietary and physical activity habits, and mental balance.

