### 7.4 Sample size calculation

The endpoint well-being will be assessed using the WHO-5 Well-being Index (34). In our pilot study the mean score at baseline was 55. The instrument has to our knowledge not been applied on a general Swedish population. In Danish general population surveys, the mean WHO-5 score was 60-70 ( $sd=19.0-19.9$ ) (36, 47, 48). A change of 10-20 points in WHO-5 has been proposed as a clinically relevant change (36, 49). In up-scaled interventions 60% lower effects are expected (50). We therefore aim at a difference of 12 points in the score between intervention groups and control group as well as between baseline and 6 months. A fluctuation in well-being is considered normal (36), subjects with well-being score  $>70$  are not expected to improve and will be excluded from the analysis. In the pilot study 21% of participants reached 70 points at baseline.

Desirable sample size was calculated to detect an effect of 12 points (36, 51) based on the assumption of two-tailed testing, an alpha error  $\alpha=0.05$  and power  $1-\beta=0.90$  and  $sd=19.9$  (48). To detect a medium standardised effect size of 0.5 (Cohen's d) for the primary outcome well-being at 6 months a sample size of at least 25 subjects per group is recommended. Expected drop-out rate due to withdrawal and lost to follow-up at six months is 75 %. Based on the expected drop-out rates and on excluding 20% from the analysis due to baseline score  $>70$ , we need to recruit at least 500 subjects to assure 25 subjects in each intervention arm. In the control group we assume subjects to be excluded based on using a digital product for behavior change and strive to include 200 subjects.

The secondary outcomes are exploratory due to the person-centred design of the service. The subjects will set individual goals and possibly change goals during the intervention. Likewise, habits and behavior change are largely changeable due to circumstances. The current research is not immense enough to guide a decision for minimal expected effects when individual goals are set (e.g., reducing weekly servings of red meat). A larger sample size than what is required for the primary

endpoint well-being is desired. Similarly, the secondary analyses of mediating factors and responsiveness require a large sample size. We therefore aim to include 5000 subjects.

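### The primary WHO-5 model names only intervention level and time, with no group-by-time term and no confounder adjustment, for a comparison whose arms are self-chosen

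*Protocol*

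**What the plan says.** The synopsis (1.6) calls the study a "Post-market observational clinical investigation with a control group (a quasi-experimental study". Section 3.1 explains why nobody is randomised: "the users or their employers will pay for the digital service and thus choose the level of support". The primary objective (5.1) is nevertheless effectiveness on well-being against a control sample of the general population.

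Section 6.2.1 aims recruitment of users at people who need lifestyle change and recruits controls through social media. Section 13 adds large companies as a source of controls. Section 6.2 excludes controls who already use other support for behaviour change.

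Section 7.3 says that change in well-being and the intermediate outcomes "will be analysed across time and between groups using mixed model for repeated measures", and continues: "The model will include intervention level and time (0, 6, 12, 18 and 24 months". Demographic factors appear in the next paragraph of 7.3, in separate association models, and in objective IV. Hypothesis 1 (5.3) is a difference of at least 12 points in mean score at 6 months.

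The information needed for adjustment is largely planned. Section 6.3.2 lists "Demographics: age, gender, occupational status, profession, education, country of origin and living area". Table 1 schedules these at month 0, together with WHO-5 and readiness to change (RTCQ). It does not say which items controls answer.

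**The concern.** In a non-randomised comparison the model terms carry the burden that randomisation would otherwise carry. Here the people who sign up are, by the protocol's own aim, those who want or need change, while controls have not sought such support. The groups can differ in starting well-being, age, gender, education, occupation and motivation before anyone opens the app. A model with intervention level and time alone cannot separate the app from those differences. A larger user arm does not help, because it only narrows the interval around a biased estimate.

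There is a second gap. Without a group-by-time term the model has one group effect for all visits, including month 0, so it does not contain a 6-month difference as a parameter. Hypothesis 1 and 7.3 also point to different contrasts (6-month means and change), and in non-randomised groups these can disagree. The only acknowledgement of selection bias, in 6.3.1, concerns who answers questionnaires, not who is in which group.

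**Working it through.** **Inputs from the protocol (7.4 unless stated).** Users: "In our pilot study the mean score at baseline was 55". General population: "In Danish general population surveys, the mean WHO-5 score was 60-70", SD 19.0-19.9. Target difference 12 points. Scores above 70 are excluded from the primary analysis in both groups (6.2). Planned enrolment is 5000 users and 200 controls, with about 20% excluded for scores above 70 and 75% drop-out at 6 months.

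**Assumptions added here.** Baseline scores are normal, and the Danish means stand in for the controls.

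**1. Gap before exclusion.** 60 - 55 = 5 and 70 - 55 = 15 points.

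**2. Gap after excluding scores above 70.** Means of a normal distribution restricted to 0-70, SD 19.9:

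| Mean before exclusion | Mean after | Gap to users | Share of 12 points |
|---|---|---|---|
| 55 (users) | 47.5 | - | - |
| 60 | 50.0 | 2.5 | 21% |
| 65 | 52.2 | 4.7 | 39% |
| 70 | 54.2 | 6.7 | 56% |

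With SD 19.0, or without the lower limit at 0, the gap runs from 2.6 to 6.9 points (6.9/12 = 58%).

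**3. What the gap does under each reading of the analysis.**

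- *Raw 6-month means.* If the gap g persisted unchanged, the contrast would be the app effect minus g, a bias of 2.5 to 7 points against the app.
- *Difference in change.* A constant gap cancels, but differential regression to the mean does not. Take an assumed baseline to 6-month correlation of 0.5. If both groups regress to one common mean, the bias is (1 - 0.5) x g, or 0.5 x 2.5 = 1.3 to 0.5 x 6.7 = 3.4 points in favour of the app. If each group regresses to its own mean, users rise by 0.5 x (55 - 47.5) = 3.8 and controls by 0.5 x (60 - 50.0) = 5.0 to 0.5 x (70 - 54.2) = 7.9. The bias is then 1.2 to 4.1 points against the app. The direction depends on something the data may not settle.
- *Group and time main effects only.* Controls contribute data for about 7 months (section 15). With equal weight on months 0 and 6, a true 12-point effect and no baseline gap, the single group coefficient averages 0 and 12 and gives 6.

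**4. Effect on the error rate (illustration).** Analysable users: 5000 x 0.8 x 0.25 = 1000. Analysable controls: 200 x 0.8 x 0.25 = 40 if they drop out like users, or 200 x 0.8 = 160 if none do; control drop-out is an assumption. SE = 19.9 x sqrt(1/1000 + 1/n_control), which is 3.21 with 40 controls and 1.69 with 160. With no app effect and a residual group difference b, the chance of p < 0.05 is P(|Z + b/SE| > 1.96):

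| b | 40 controls | 160 controls |
|---|---|---|
| 3 points | 15% | 42% |
| 5 points | 34% | 84% |

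Here b is any uncontrolled difference, in either direction, that remains in the chosen contrast.

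**The case against.** The strongest reply is that baseline well-being is already handled. Month 0 is among the listed times, so baseline WHO-5 is in the model as a repeated response; 7.3 speaks of change, and 7.2 reports change from baseline by group. This stands. A reader might infer that no baseline variable is taken into account at all, and the protocol does not support that for WHO-5. What remains is that the term needed to express a difference in change is not named, and that demographics and motivation are not handled under any reading.

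A reader might also take the unrestricted gap of 5 to 15 points as the bias (5/12 = 42% to 15/12 = 125% of the target). That ignores the exclusion of scores above 70 in both groups. Nor does the protocol show that users must improve by the target plus the gap, or that the starting gap decides the sign of the result. Both would need raw 6-month means to be the analysis, which 7.3 does not say.

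The gap itself is an extrapolation. It sets a small Swedish pilot against Danish surveys, and the real controls are volunteers whose baseline is unknown. Most pilot participants (94%) also came through social media, so the groups may be more alike than the figures suggest. Demographic imbalance is plausible, but the protocol gives no control demographics to show it.

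Finally, a statistical analysis plan may add covariates, and saying what a model will include does not exclude other terms. That is fair, but the protocol goes beyond silence: it lists the terms for the primary comparison and places demographics in separate analyses.

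**Conclusion.** The concern holds in this form: the primary model as written has no group-by-time term and no adjustment for demographic or motivational confounders, although allocation is by choice and payment and the stated aim is effectiveness. The contrast is also unsettled between 6-month means and change. Following the text as it stands gives an estimate open to confounding, of unknown size and direction.

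The protocol's figures allow a baseline gap of about 2.5 to 7 points after the exclusion, given normal scores, SD 19.0-19.9 and Danish means for the controls. That gap enters fully only if raw 6-month means are compared. Under a change contrast a constant gap drops out, leaving differential regression to the mean (about 1 to 3.5 points in favour of the app or 1 to 4 against it, at an assumed correlation of 0.5) and confounding by age, gender, education, occupation and motivation, which cannot be sized from the protocol.

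**What to change.** In 7.3, add a group-by-time term. Prespecify that the 6-month intervention-control contrast is adjusted for baseline WHO-5, age, gender, education, occupation, living area and country of origin, and for RTCQ motivation if controls answer it. Propensity or overlap weights built from the same variables are an acceptable alternative. State whether the adjusted 6-month difference or the adjusted difference in change is primary, report the other as a sensitivity analysis, and reword Hypothesis 1 to match.

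Confirm that the control survey carries these items. Section 6.3.2 describes collecting demographics at sign-up, and Table 1 does not separate controls from users. If items are missing, the survey must be changed before controls complete their baseline questionnaire.

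The cost is otherwise wording. Adjustment uses a few degrees of freedom in a control group that may have as few as about 40 analysable subjects, so the list should stay short or weights should be used. Unmeasured confounding remains and should be stated as a limitation.

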### 5.3 Hypotheses

1. The mean well-being score at 6 months of intervention is  $\geq 12$  score points higher in the intervention groups compared to the control group.
2. The impact on well-being is slightly stronger in the groups with higher level of support (Standard and Premium) compared to the group with lower level of support (Basic).
3. The medical device improves the individually targeted dietary habits, physical activity, and mental health among users at 6 months intervention compared to start of intervention.
4. Motivation, self-efficacy and achieving the self-identified goal mediate the effects of using the digital service on dietary and physical activity habits, mental health, and well-being.
5. The engagement with the service levels of across 24 months intervention for the group with less support (Basic) but maintains in the two groups with higher level of support (Standard and Premium).
6. The intervention effects on behavior change and well-being are maintained over 24 months in the two groups with higher levels of support (Standard and Premium) compared with the group with less support (Basic).

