## 7. Statistical design and analysis

### 7.1 Analysis population

For the endpoint well-being an intention-to-treat approach will be applied. By using mixed model for repeated measures all subjects with two or more measurements will be included in the analysis and manual imputation is not needed. For the intermediate outcomes dietary habits, physical activity, and mental health only subjects who have set up change goals within the area will be analysed.

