## 15. Suspension or premature termination of the clinical investigation

The intervention subjects are included in the research study and contributing with data until 25 months have passed since registration of the first activity, or until reporting a wish to withdraw. Control subjects are included in the research study and contributing with data until 7 months have passed since submitting the first questionnaire, or until reporting a wish to withdraw. Reasons to terminate the research study are if large quantities of complaints are made about the digital service or about the burden of answering questions, or if 5000 subjects are not reached within 5 years.

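### The model terms listed for the primary analysis include no group-by-time term and no month-6 contrast, so read literally they do not estimate the 6-month difference from control

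*Protocol*

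**What the plan says.** The synopsis (section 1.6) gives the primary endpoint as "Well-being at 6 months". Hypothesis 1 in section 5.3 concerns the same time point: "The mean well-being score at 6 months of intervention is" at least 12 points above control. Section 7.4 repeats the target (the last number quoted is the month of follow-up): "We therefore aim at a difference of 12 points in the score between intervention groups and control group as well as between baseline and 6".

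Section 7.3 says that change in well-being "will be analysed across time and between groups using mixed model for repeated measures, and reported as estimates with confidence intervals". It then lists the contents of the model: "The model will include intervention level and time (0, 6, 12, 18 and 24 months"). No interaction is written and none is ruled out. No contrast is singled out as the primary result.

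Section 7.1 sets who enters the model: "all subjects with two or more measurements will be included in the analysis and manual imputation is not needed".

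Section 15 sets different follow-up for the two sides. For controls: "Control subjects are included in the research study and contributing with data until 7 months have passed since submitting the first questionnaire". Intervention subjects go on "contributing with data until 25 months have passed since registration of the first activity". Of the visits listed for the model, only months 0 and 6 can have control data.

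**The concern.** In a repeated-measures model with month 0 among the outcomes, a main effect of group is a single shift applied to every visit. The service can have no effect at baseline, so this shift mixes a pre-treatment difference with the 6-month difference that the study is about. The between-group estimate at month 6, and any differential change, comes from the group-by-time term, and that is the term not listed.

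This matters more here than in a randomised trial. Users choose and pay for their level of support (section 3.1), so equal baselines cannot be presumed. Section 7.4 gives a pilot baseline mean of 55, against 60-70 in Danish general-population surveys. A baseline gap would be carried directly into the reported effect.

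**Working it through.** **Figure in the plan.** The protocol gives no figure for what this model estimates. The only related number is the 12-point target (sections 5.3 and 7.4), used below as the true 6-month difference.

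**Inputs**
- Visits 0, 6, 12, 18 and 24 months (section 7.3); controls at 0 and 6 only (section 15).
- SD 19.9 (section 7.4), taken as equal at all visits unless stated. This is an assumption.
- Within-person correlation r = 0.3, 0.5 or 0.7. This is an assumption; the protocol gives none.
- Intervention levels pooled, and every subject has both months 0 and 6.

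**Formula.** Let d0 and d6 be the true group differences at months 0 and 6, and s0 and s6 the SDs. With group and categorical time as the only terms, months 12-24 each have their own time parameter and no controls, so they carry no information on the group coefficient. Its expectation is then

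(1 - w) x d0 + w x d6, where w = (s0² - r s0 s6) / (s0² + s6² - 2 r s0 s6).

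If s0 = s6, then w = 1/2 for any r.

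**Equal baselines, equal variances** (d0 = 0, d6 = 12): 0.5 x 0 + 0.5 x 12 = **6.0** for r = 0.3, 0.5 and 0.7. A full generalised-least-squares calculation with 5000 users at all five visits and 200 controls at two also gives 6.0.

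**Unequal baselines, equal variances, d6 = 12**

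| d0 | Calculation | Group coefficient |
|---|---|---|
| -10 | (-10 + 12)/2 | 1.0 |
| -5 | (-5 + 12)/2 | 3.5 |
| +5 | (5 + 12)/2 | 8.5 |

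**Narrower baseline.** Excluding baseline scores above 70 cuts the spread at month 0 but not directly at month 6. Take s0 = 12 (an assumption; the protocol gives no truncated SD), s6 = 19.9 and d0 = 0. Then s0² = 144, s6² = 396.01 and s0 s6 = 238.8.

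| r | w | 12 x w |
|---|---|---|
| 0.3 | (144 - 71.64)/(540.01 - 143.28) = 0.182 | 2.2 |
| 0.5 | (144 - 119.4)/(540.01 - 238.8) = 0.082 | 1.0 |
| 0.7 | (144 - 167.16)/(540.01 - 334.32) = -0.113 | -1.4 |

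**Does the 24-month span matter?** With months 12-24 dropped, the main-effects coefficient is still 6.0. With all visits kept and group-by-time added, the contrast is 0.0 at month 0 and **12.0** at month 6. The missing term drives the result; the length of follow-up does not.

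**The case against.** The strongest reply is that section 7.3 is a short list of terms and not an exclusive specification. The preceding sentence says that change is analysed over time and between groups, which a main-effects model with month 0 as an outcome cannot do. The stated aim therefore suggests an interaction, and a statistical analysis plan that is not at hand may specify one. This stands to a point: the protocol does not exclude the interaction, and it cannot be said that the wrong model will be fitted. But the protocol chose to state the contents of its primary model, and what it states does not yield its own primary endpoint. That goes beyond detail left for later.

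Three stronger readings are tempting and are not supported.
- A reader might infer that the analysis will report half the true effect. That holds only with main effects alone, equal baselines, equal variances at months 0 and 6, and subjects seen at both visits. The protocol's own figures and its exclusion of scores above 70 put the equal baselines and variances in doubt.
- A reader might blame a 24-month model when controls stop at 7 months. The calculation shows otherwise, and sections 7.3 and 15 do not conflict: 7 months covers the primary visit, and hypotheses 5 and 6 compare the intervention levels with each other.
- A reader might add an inflated error rate from testing three levels against one control. Whether the primary test is pooled or by level is a separate question, and the protocol does not give the level sizes needed for such a figure.

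**Conclusion.** The point holds in a conditional form. If the listed terms are the whole model, its group coefficient is not the 6-month difference from control. Across the cases above it ranges from about -1.4 to 8.5 points for a true difference of 12. The value 6.0 is one case in that range, resting on equal baselines and variances. The 8.5 and 1.0 to 3.5 figures rest on assumed baseline gaps, and the 2.2 to -1.4 figures on an assumed baseline SD of 12. That the two listed terms cannot isolate month 6 depends on none of these assumptions. Adding the interaction resolves it fully. The absence of controls after 7 months needs a clarifying sentence but is not a source of bias in the 6-month result.

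**What to change.** In section 7.3:
1. Add the group-by-time interaction to the model.
2. Name the month-6 contrast with control as the primary estimate, and say whether it is adjusted for baseline or is the difference in change from 0 to 6 months. Choose one in advance, because in self-selected groups they need not agree. For example, with differences of -5 at month 0 and +7 at month 6, the difference in change is 7 - (-5) = 12. A baseline-adjusted contrast lies between 7 and 12 for any adjustment slope between 0 and 1.
3. State that comparisons with control end at month 6, and that comparisons at 12-24 months are among the three intervention levels only.

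The cost is two or three sentences and a few more model parameters. Data collection does not change.
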